## Abstract

**Background:**

In Tunisia, the number of cardiac implantable electronic devices (CIEDs) is increasing, owing to the increase in patient life expectancy and expanding indications. Despite their life-saving potential and a significant reduction in population morbidity and mortality, their increased numbers have been associated with the development of multiple early and late complications related to vascular access, pockets, leads, or patient characteristics.

**Objective:**

The study aims to identify the rate, type, and predictors of complications occurring within the first year after CIED implantation. It also aims to describe the demographic and epidemiological characteristics of a nationwide sample of patients with CIED in Tunisia. Additionally, the study will evaluate the extent to which Tunisian electrophysiologists follow international guidelines for cardiac pacing and sudden cardiac death prevention.

**Methods:**

The Tunisian National Study of Cardiac Implantable Electronic Devices (NATURE-CIED) is a national, multicenter, prospectively monitored study that includes consecutive patients who underwent primary CIED implantation, generator replacement, and upgrade procedure. Patients were enrolled between January 18, 2021, and February 18, 2022, at all Tunisian public and private CIED implantation centers that agreed to participate in the study. All enrolled patients entered a 1-year follow-up period, with 4 consecutive visits at 1, 3, 6, and 12 months after CIED implantation. The collected data are recorded electronically on the clinical suite platform (DACIMA Clinical Suite).

**Results:**

The study started on January 18, 2021, and concluded on February 18, 2023. In total, 27 cardiologists actively participated in data collection. Over this period, 1500 patients were enrolled in the study consecutively. The mean age of the patients was 70.1 (SD 15.2) years, with a sex ratio of 1:15. Nine hundred (60%) patients were from the public sector, while 600 (40%) patients were from the private sector. A total of 1298 (86.3%) patients received a conventional pacemaker and 75 (5%) patients received a biventricular pacemaker (CRT-P). Implantable cardioverter defibrillators were implanted in 127 (8.5%) patients. Of these patients, 45 (3%) underwent CRT-D implantation.

**Conclusions:**

This study will establish the most extensive contemporary longitudinal cohort of patients undergoing CIED implantation in Tunisia, presenting a significant opportunity for real-world clinical epidemiology. It will address a crucial gap in the management of patients during the perioperative phase and follow-up, enabling the identification of individuals at particularly high risk of complications for optimal care.

**Trial Registration:**

ClinicalTrials.gov NCT05361759; https://classic.clinicaltrials.gov/ct2/show/NCT05361759

**International Registered Report Identifier (IRRID):**

RR1-10.2196/47525

## Introduction

### Background

Cardiac implantable electronic devices (CIEDs), including permanent pacemakers (PMs), implantable cardioverter defibrillators (ICDs), and cardiac resynchronization therapy devices with or without defibrillators (CRT-Ds or CRT-Ps), are standard therapy for bradyarrhythmia, tachyarrhythmia, and systolic heart failure [1,2]. Their use has increased over the last decade [3,4]. However, CIED implantation comes with a considerable burden of complications, leading to elevated patient morbidity, health care costs, and mortality [5-8]. The most recent consensus on device implantation and replacement by the European Heart Rhythm Association [9] has been significantly influenced by the invaluable contributions of various international registries. One of the most prominent among them is the “Replace” registry [10], which has played a pivotal role in advancing our understanding of this crucial aspect of cardiac care.

A comprehensive understanding of post-CIED implantation complications and their predictive factors is essential for patient management when considering CIED implantation. Therefore, a survey of patients undergoing CIED implantation in Tunisia is crucial to identify specific CIED complications due to the demographic and epidemiological specificities of the patients, as well as the conditions of the local health care system.

### Study Aims

This study aims to assess the incidence, characteristics, and predictors of complications arising in the initial 12 months following the implantation of CIEDs, describe the demographic and epidemiological profiles of a national cohort of consecutive patients with CIED, and provide insights into the level of compliance exhibited by Tunisian electrophysiologists with international guidelines pertaining to cardiac pacing and the prevention of sudden cardiac death.

## Methods

### Study Design and Patients’ Enrollment

NATURE-CIED (National Study of Cardiac Implantable Electronic Devices) is a nationwide, multicenter, prospective observational study with a 1-year follow-up period. The study’s steering committee extended invitations to all electrophysiologists, interventional cardiologists, and cardiovascular surgeons with experience in CIED implantation, regardless of whether they are practicing in the Tunisian public or private sectors, to participate in the study.

Patients’ enrollment occurred between January 18, 2021, and February 18, 2022, at all Tunisian public and private CIED implantation centers that agreed to participate in the study. Eligibility screening was conducted during hospitalization.

The study population consisted of consecutive patients undergoing primary CIED (conventional PMs, ICDs, and cardiac resynchronization: CRT-P–CRT-D) implantation, generator replacement, and upgrade procedure. To be enrolled, eligible patients have to provide written informed consent. All enrolled patients entered a 1-year follow-up period with 4 consecutive visits at 1, 3, 6, and 12 months after the CIED implantation. Exclusion criteria are nonconsenting patients and those operated exclusively for lead dysfunction.

### Data Sources

A steering board with 2 main investigators pre-established a specific case report form (CRF) for each type of CIED. Baseline data included patient demographics, ethnic specificity, medical history, cardiovascular history, cardiovascular risk factors, the CIED implantation indication, vital signs, laboratory measurements, electrocardiographic and echocardiographic findings, details of medical management, and results of eventual invasive and noninvasive investigations prior to CIED implantation (echocardiography, Holter monitoring, treadmill exercise stress test, and electrophysiological study).

The form also includes data regarding the technical aspects of the CIED implantation procedure and the occurrence of any periprocedural complications. Finally, the form specifies data on the clinical follow-up and device electrical testing parameters, as well as the eventual major incident events and CIED complications during the follow-up period. Investigators (electrophysiologists and interventional cardiologists) who agreed to participate in the study were asked to complete the pre-established form (CRF) for each type of implanted device at the enrollment visit and each scheduled visit.

Collected data were electronically recorded on a clinical suite platform (DACIMA software), which complies with international standards including US FDA 21 CRF part 11 (Food and Drug Administration 21 Code of Federal Regulations Part 11), US HIPAA (Health Insurance Portability and Accountability Act) and ICH (International Conference on Harmonisation), and Medical Dictionary for Regulatory Activities. The main investigators and the DACIMA consulting team periodically validated recorded data. The clinical suite platform generates alerts and requests in case of inconsistencies and missing data. Throughout the planned duration of the study, the steering board supervises the inclusion of patients, checks the data sources, and prepares the study’s statistical analysis plan.

### Timeline

Patient enrollment and data collection began on January 18, 2021, and continued until February 18, 2022. Follow-up continued until all patients had 1-year data. The end of the study was therefore scheduled for February 18, 2023 (Figure 1).

**Figure 1 figure1:**
[figure not shown]
The Timeline of the Nature CIED study.

If patients missed a scheduled follow-up visit, they or their relatives were contacted by phone to assess any adverse event and to reschedule a follow-up appointment.

### Outcomes

The main objective of this observational study is to assess the incidence, characteristics, and predictors of major and minor complications arising in the initial 12 months following the implantation of CIEDs.

The complications were characterized as major when life-threatening or requiring surgical reintervention for correction, and minor when suitable for treatment on an outpatient basis, involving device reprogramming, or requiring exclusive clinical observation [11]. Major complications include implantation failure, lead-related reinterventions, tamponade or myocardial perforation, pneumothorax requiring drainage, hematoma requiring evacuation, wound or pocket infection, systemic infections or endocarditis, Twiddler syndrome, and procedure-related deaths. Minor complications include pacing threshold increase, phrenic nerve stimulation, heart failure or left ventricular ejection fraction decrease, pericardial effusion, and conservatively treated hematoma and pneumothorax.

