### Statistical Analysis

The DACIMA Clinical Suite platform enables the collection of web-based data and their extraction in SAS (SAS Institute) or SPSS (IBM Corp) format. The statistical analysis is exploratory, involving the calculation of 95% CI. The data will be described for the whole analyzed population. Continuous variables will be described by mean and SD or median and IQR. Categorical variables will be described by the size and frequency of every modality. Mean comparison will be performed by analysis of variance or by nonparametric tests if the hypothesis of normality is rejected.

The normality of continuous variables will be verified with the Shapiro-Wilk test. The statistical tests are bilateral with a 95% CI. A chi-square test will be performed for categorical variables. Yates correction or the Fisher exact test will be used if the conditions of validity for the chi-square test are not met.

A multivariate analysis will be performed with each complication as a dependent factor. The independent variables will be age, gender, ethnic specificity, BMI, CIED type, procedure type, procedure priority, implantation center (private and public), and CIED implanting operator whether he is an electrophysiologist or not (interventional cardiologist or cardiac surgeon).

Univariate logistic regression will be carried out with a 10% output threshold. The final model will be performed with the parameters selected by the backward stepwise method of Wald. The selected variables in the final model will be tested at the 5% threshold. The interaction between selected parameters is tested at the 10% threshold. The intermediate analyses will be carried out after formulating the statistical analysis plan.

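### Heart failure or LVEF decrease counts as a minor complication with no new-onset or device-relatedness condition and is modelled on device type without baseline heart failure, LVEF or indication

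*Protocol article*

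**What the plan says.** The main objective (Protocol article, Outcomes) is to "assess the incidence, characteristics, and predictors of major and minor complications arising in the initial 12 months". An event is "minor when suitable for treatment on an outpatient basis, involving device reprogramming, or requiring exclusive clinical observation". The list that follows reads "Minor complications include pacing threshold increase, phrenic nerve stimulation, heart failure or left ventricular ejection fraction decrease, pericardial effusion", with conservatively treated hematoma and pneumothorax added at the end. Deaths appear in the list of major events with a qualifier: "Twiddler syndrome, and procedure-related deaths".

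The Background says that the devices under study "are standard therapy for bradyarrhythmia, tachyarrhythmia, and systolic heart failure".

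The Statistical Analysis section says: "A multivariate analysis will be performed with each complication as a dependent factor". The candidate predictors are "age, gender, ethnic specificity, BMI, CIED type, procedure type, procedure priority, implantation center (private and public") and whether the operator is an electrophysiologist, nine in all. Baseline heart failure, LVEF and implantation indication are not among them. Data Sources states that cardiovascular history, the indication and echocardiographic findings are recorded at baseline.

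**The concern.** Of the listed complications, this is the one that the article also names as a reason for implanting a device. The rule for a minor event concerns management, not cause. A patient implanted for systolic heart failure whose condition later worsens, and who is treated as an outpatient, therefore meets the definition even if neither the procedure nor pacing played any part.

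Two results are exposed. The first is incidence: disease course adds to the minor count and to any overall complication rate. The second is prediction: in the model with heart failure/LVEF decrease as the outcome, device type partly stands in for heart failure already present at implantation, and the named candidates cannot separate the two. The article intends the results to identify high-risk patients and to inform a national peri-implantation protocol, so a device-type effect that reflects the indication would mislead both uses.

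**Working it through.** **Is there a figure to reproduce?** No. The article gives no expected event rate, sample size calculation or power, so the check has two parts: what the text implies, and an illustration of size.

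**Text.**
1. Outcomes: heart failure or LVEF decrease is a minor complication, limited only by management.
2. Background: systolic heart failure is an indication.
3. Statistical Analysis: each complication is modelled, device type is a candidate, and baseline heart failure, LVEF and indication are not.

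Together these give confounding by indication in one model, provided that background heart failure is more frequent in CRT/ICD recipients. That proviso is clinically plausible, but the article gives no data on it.

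**Inputs from the Results section.** Conventional pacemaker 1298, CRT-P 75, ICD 127 (45 of them CRT-D). Check: 1298 + 75 + 127 = 1500. CRT/ICD group: 75 + 127 = 202, and 202/1500 = 13.5%. ICDs without CRT: 127 − 45 = 82.

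**Assumptions (not in the article).** There is no true device effect. The 12-month background rate of heart failure/LVEF decrease is h_P in pacemaker patients and h_D in CRT/ICD patients. True complications occur at one rate c in every device type, independently of background heart failure. I take c = 4% to 10%, the range that the Discussion quotes for pacemakers.

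**Heart failure/LVEF model.** Spurious OR = [h_D/(1 − h_D)] / [h_P/(1 − h_P)].
- 2% v 2%: OR = 1.0.
- 2% v 5%: (0.05/0.95)/(0.02/0.98) = 0.0526/0.0204 = 2.58. A two-sided 5% comparison of 1298 with 202 patients flags this with probability 0.68.
- 2% v 10%: (0.10/0.90)/(0.02/0.98) = 0.1111/0.0204 = 5.44, flagged with probability 0.99.

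**Pooled incidence.** In each group P(any) = 1 − (1 − c)(1 − h), and the overall rate is (1298·P_P + 202·P_D)/1500. Example with c = 4% and 2% v 10%: P_P = 1 − 0.96 × 0.98 = 0.0592; P_D = 1 − 0.96 × 0.90 = 0.136; overall = (76.8 + 27.5)/1500 = 7.0%.

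| h_P v h_D | c = 4% becomes | c = 10% becomes |
|---|---|---|
| 2% v 2% | 5.9% | 11.8% |
| 2% v 5% | 6.3% | 12.2% |
| 2% v 10% | 7.0% | 12.8% |

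Over these cases the inflation is about 1.8 to 3.0 percentage points. It is present even when the background rates are equal.

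**The case against.** The article condenses a fuller protocol. A case report form was prepared for each device type, and Data Sources lists major events and device complications as separate items on the follow-up form. The major/minor scheme is taken from a cited source that is not at hand. Other listed items, such as pericardial effusion and endocarditis, also carry no relatedness wording, so the qualifier on deaths proves little alone. The analysis is described as exploratory.

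Part of this stands: the form may hold what is needed to separate the events. It does not undo the explicit classification in Outcomes, and the candidate predictors are named. Pericardial effusion and endocarditis are not given in the article as reasons for implantation; heart failure is.

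A reader might infer four stronger things that the article does not support.
- **That any heart failure in the first year counts.** Minor events are limited to those managed as outpatients, by reprogramming or by observation. An admission that is neither life-threatening nor followed by reintervention fits neither class.
- **That CRT/ICD recipients would be labelled high risk for device complications in general.** Each complication is modelled separately and no pooled regression is stated, so the lead, pocket and infection models are not touched. Device type is also a candidate subject to screening and backward selection, not a fixed term.
- **That LVEF falls would be found mainly in patients imaged for symptoms.** The article says "the form specifies data on the clinical follow-up and device electrical testing parameters", which neither includes nor excludes echocardiography at follow-up.
- **That the device-type effect is about fivefold.** Any such ratio is one assumed rate divided by another. The article gives no heart failure rate by device, and does not say how many of the 82 non-CRT ICD recipients had heart failure, with tachyarrhythmia also a stated indication.

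**Conclusion.** The point holds in a limited form. As published, the definition lets pre-existing heart failure that worsens and is managed conservatively count as a minor complication, and the named candidates leave device type confounded by indication in the heart failure/LVEF model. The pooled minor and overall rates can be inflated; models for other complications are not affected.

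The size is not derivable from the article. The odds ratios of about 2.6 to 5.4 and the inflation of about 1.8 to 3.0 points rest on assumed background rates and on no true device effect. The odds-ratio bias disappears if background rates do not differ by device type. Some of these events, for example pacing-induced ones, are truly device-related, so removing the component outright would also be wrong.

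**What to change.** The Results section says that detailed analyses are still pending, so the change can be made before they are reported.

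1. Report heart failure/LVEF decrease as a separate clinical event, by device type and by baseline heart failure/LVEF.
2. Give the minor and overall complication rates with and without it.
3. Count it as a complication only when it is new relative to baseline and recorded as device- or pacing-related, where the case report form holds that information. Where it does not, rely on steps 1 and 2 and avoid attributing events in retrospect.
4. Add baseline heart failure/LVEF or indication, already collected, as a covariate in its model.

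The cost is outcome wording, recoding of recorded events and one more covariate. Events for that model may be few: at the assumed 2% v 5% to 2% v 10%, about 26 + 10 = 36 to 26 + 20 = 46, against nine candidates already. The downside is a lower headline minor-complication count and less direct comparison with reports that include heart failure; giving rates both ways reduces the latter.

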### Ethical Considerations

The study was performed according to the ethical principles for medical research involving human subjects specified in the Declaration of Helsinki and the ICH Good Clinical Practices. Ethics approval was obtained from the human research ethics committees at Abderrahmen Mami Hospital in Tunis (04/2021). Written informed consent was obtained from all the patients who participated in the study. The protocol of NATURE-CIED was approved by the Tunisian Society of Cardiology and Cardiovascular Surgery. The NATURE-CIED study was submitted to ClinicalTrials.gov (NCT05361759).

### Statistical Analysis

The DACIMA Clinical Suite platform enables the collection of web-based data and their extraction in SAS (SAS Institute) or SPSS (IBM Corp) format. The statistical analysis is exploratory, involving the calculation of 95% CI. The data will be described for the whole analyzed population. Continuous variables will be described by mean and SD or median and IQR. Categorical variables will be described by the size and frequency of every modality. Mean comparison will be performed by analysis of variance or by nonparametric tests if the hypothesis of normality is rejected.

The normality of continuous variables will be verified with the Shapiro-Wilk test. The statistical tests are bilateral with a 95% CI. A chi-square test will be performed for categorical variables. Yates correction or the Fisher exact test will be used if the conditions of validity for the chi-square test are not met.

A multivariate analysis will be performed with each complication as a dependent factor. The independent variables will be age, gender, ethnic specificity, BMI, CIED type, procedure type, procedure priority, implantation center (private and public), and CIED implanting operator whether he is an electrophysiologist or not (interventional cardiologist or cardiac surgeon).

Univariate logistic regression will be carried out with a 10% output threshold. The final model will be performed with the parameters selected by the backward stepwise method of Wald. The selected variables in the final model will be tested at the 5% threshold. The interaction between selected parameters is tested at the 10% threshold. The intermediate analyses will be carried out after formulating the statistical analysis plan.

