## Results

In total, 27 investigators, comprising 14 from the public sector and 13 from the private sector, volunteered to take part in the study. It is worth noting that some of the investigators were involved in both the public and private sectors. A total of 1500 consecutive patients were enrolled for a 12-month follow-up period following CIED implantation. Sixty percent (n=900) of the patients were from the public sector, while 40% (n=600) were from the private sector. The patients’ mean age was 70.1 (SD 15.2) years, with a sex ratio of 1:15. A total of 1298 (86.3%) patients received a conventional PM and 75 (5%) patients received a biventricular pacemaker (CRT-P). ICDs were implanted in 127 (8.5%) patients. Of these patients, 45 (3%) underwent CRT-D implantation. The detailed analyses of this study are currently under investigation and will be published elsewhere in the near future.

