## Discussion

### Summary

To the best of our knowledge, NATURE-CIED is the first National study of CIEDs in North Africa to provide the combination of large numbers of patients and devices and diverse implanting physicians. Twenty-seven cardiologists (electrophysiologists and interventional cardiologists) enrolled 1500 patients who underwent CIED implantation.

According to the second report from the Pan African Society of Cardiology working group on cardiac arrhythmias and pacing [12], Tunisia had the highest implant rates, with 164.3 PMs per million inhabitants and 2.16 PM implantation practitioners per million inhabitants in 2018, which makes it rank in the second position after Mauritius [12].

However, there is still a gap concerning patients’ demographics, CIED indications, and conformity to recent European Society of Cardiology guidelines [2] and CIED-related complications [12-14].

Both patient-related and procedure-related predictors of complications may identify patients with a particularly high risk of complications [15]. Previously reported incidences of complications after CIED implantation varied widely because of differences in the definitions of complications and length of follow-up [15-18]. Several previous studies in the 2000s reported that complication rates for PM were 4%-10% [13,17-19] and 3%-10% for ICDs and CTRDs [6,20]; however, an analysis of US Medicare states that data in 2014 showed much lower complication rates [21].

In 2010, the “Replace” registry, comprising data from a substantial cohort of 1744 patients who underwent device replacement procedures, yielded pivotal insights into predictive factors for complications [10]. This comprehensive analysis has, in turn, informed the development of practical and evidence-based procedural recommendations. By identifying the key determinants of complications, the registry has empowered health care professionals to more effectively anticipate and mitigate risks, ultimately leading to improved patient outcomes.

Therefore, the NATURE CIED study aims to offer detailed and comprehensive data on the predictors of CIED complications during the perioperative and 1-year follow-up period, which are derived from real-world data in Tunisia. The information generated by this study will prove valuable in the development of a national peri-implantation management protocol and the assessment of overall health care costs [11,12,14,22].

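### Predictor models are stated only for each single complication, most of which are likely too rare for nine candidates with stepwise selection, and no model is stated for the major and minor outcomes of the main objective

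*Protocol article*

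**What the plan says.** The Outcomes section of the protocol article sets the main objective as the incidence, characteristics and "predictors of major and minor complications arising in the initial 12 months following the implantation of CIEDs". It then lists the types in each class. There are nine major types, the list beginning "Major complications include implantation failure, lead-related reinterventions, tamponade or myocardial perforation, pneumothorax requiring drainage, hematoma requiring evacuation, wound or pocket infection". There are five minor types, or six if conservatively treated hematoma and pneumothorax count separately.

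The Statistical Analysis section fixes the dependent variable differently: "A multivariate analysis will be performed with each complication as a dependent factor". It names nine independent variables: age, gender, ethnic specificity, BMI, device type, procedure type, procedure priority, public or private center, and whether the operator is an electrophysiologist. Selection is by a univariate logistic screen at 10%, then backward Wald elimination with a final test at 5%. Interactions among selected variables are tested at 10%. The same section calls the analysis exploratory.

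The Results section gives the sample size: "A total of 1500 consecutive patients were enrolled for a 12-month follow-up period following CIED implantation". No event count appears anywhere in the article. The only rates are in the Discussion (Summary), where earlier studies "reported that complication rates for PM were 4%-10% [13,17-19] and 3%-10% for ICDs and CTRDs", followed by the remark that US Medicare "data in 2014 showed much lower complication rates".

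**The concern.** Two things do not fit together. First, the main objective concerns two classes of complication, while the stated models take complications one at a time. Second, dividing the events among 14-15 outcomes leaves few for each model, and the selection procedure is one that behaves badly with few events. Real predictors are missed. Those that pass the 5% test do so because their estimates are exaggerated, and chance findings make up a large share of what is reported.

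This matters because of the intended use. The Expected Implications section says the predictors will serve to single out high-risk patients for care. The Discussion foresees their use in a national peri-implantation management protocol. Unstable odds ratios for rare complications are a poor basis for either.

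**Working it through.** The article states no sample-size calculation, expected event count or events-per-variable target, so there is no figure of its own to reproduce.

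**Inputs**
- From the article: N = 1500; 9 candidate variables; 14-15 listed types; device mix of 1298 conventional pacemakers, 75 CRT-P and 127 ICDs, 45 of them CRT-D (so 127 − 45 = 82 other ICDs).
- Assumed: an overall complication rate of 4%-10%, borrowed from the earlier studies cited in the Discussion; one complication per affected patient; and, for parameter counts only, device type with 4 levels, procedure type with 3 and the other seven variables with 1 parameter each, giving 3 + 2 + 7 = 12.

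**Events per type**
- Patients with any complication: 1500 × 0.04 = 60 to 1500 × 0.10 = 150.
- Equal-split mean per type: 60/15 = 4.0 and 60/14 = 4.3 at the low end; 150/15 = 10.0 and 150/14 = 10.7 at the high end.
- Per candidate variable: 4.0/9 = 0.4 to 10.7/9 = 1.2. Per parameter: 4.0/12 = 0.3 to 10.7/12 = 0.9.

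**Unequal split**

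| Share of all events | Events | Events per variable (÷ 9) |
|---|---|---|
| 2% | 1-3 | 0.1-0.3 |
| 30% | 18-45 | 2.0-5.0 |
| 40% | 24-60 | 2.7-6.7 |

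Even a dominant type stays below 10 events per variable across the cited range.

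**Empty device classes.** Suppose risk is equal across devices and the four classes are kept apart. The chance that a class of size k has no event among e events is C(1500 − k, e)/C(1500, e). Inclusion-exclusion over k = 45, 75 and 82 gives the chance that at least one of the three small classes is empty: 96% at 10 events, 85% at 18 and 62% at 30. An empty class has no finite maximum-likelihood odds ratio, and the Wald statistic used for selection is then uninformative.

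**Simulation of the stated selection.** N = 1500; nine independent candidates on 12 parameters; 10% univariate Wald screen, then backward Wald at 5%; 300 runs per setting. Device mix and sector share come from the article; the other prevalences are assumed. The interaction step was not simulated. Two candidates had a true odds ratio of 2.

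| Events | True predictor selected | Share of selected that are false | Median selected OR (true 2) |
|---|---|---|---|
| 4 | 0% | 100% | none selected |
| 10 | 13% | 48% | 5.6 |
| 30 | 43% | 27% | 2.8 |
| 60 | 74% | 17% | 2.2 |
| 150 | 98% | 14% | 2.1 |

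At 10 events, for example, there were 0.243 false and 2 × 0.133 = 0.267 true selections per run, and 0.243/(0.243 + 0.267) = 48%.

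With no true predictor at all, at least one false one was reported in 13% of models at 4 events, 24% at 10, 28% at 30 and 38% at 150.

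**Position after pooling**
- Any complication: 60/9 = 6.7 to 150/9 = 16.7 events per variable.
- Major only, if half of events are major (assumption): 30/9 = 3.3 to 75/9 = 8.3.
- Ten events per variable needs 90 events, that is 90/1500 = 6.0% of patients.

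**The case against.** The strongest case against the point has four parts.

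- **The rates are background, not a planning range.** They come from older studies, and the Discussion itself says definitions and follow-up differed and that later figures were much lower. The Outcomes definition also counts events such as a rise in pacing threshold, which the older rates may not have included. Patients may also have more than one complication. The true counts could lie on either side. This stands, and the event counts above are conditional on it.
- **Not every model is sparse.** A reader might infer that every model has 4-10 events. The documents do not support that: it is an equal-split mean, and a common type could have 18-60 events. Nor does the plan fit all nine variables at once. They are candidates, and the final model keeps only those selected. Candidate counts still drive selection bias, so this softens the point without removing it.
- **The findings are not all noise.** A reader might conclude that the reported predictors will be mostly false. That holds only at the lowest counts. At about 10 events it is roughly half, and at 30 or more most selected predictors were true under the assumed odds ratio of 2. Pooling does not lower the false-positive rate of a single model either. Its gains are power, less exaggeration and fewer models.
- **The analysis is exploratory and the analysis plan is not shown.** A reader might say that the main objective is never modelled. That goes too far. The wording could be stretched to include the two classes, and the unseen plan may define them. What can be said is that the article states no such model. The exploratory label lowers the severity. It does not remove the problem, because the article intends the predictors to guide care.

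**Conclusion.** The point holds in a limited form. The stated rule (a separate model for every complication, nine candidates, univariate screen, backward Wald) is unreliable for the sparse complications, and the article states no model for the major and minor outcomes that form its main objective.

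The size rests on three assumptions: the borrowed 4%-10% rate, the split of events between types, and, for the simulation, a true odds ratio of 2 with assumed covariate prevalences. Much lower rates, as the article says were seen later, would make matters worse; a broader definition of complications could ease them. Within the cited range, no plausible type reaches 10 events per candidate variable. Estimates for an average type would be badly inflated, and real predictors would usually be missed. For a dominant type, selection is more credible but odds ratios remain somewhat inflated.

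Severity is moderate: the analysis is declared exploratory, the counts are assumed, and the correction can still be made, since the Results section says the detailed analyses are under way.

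**What to change.** In the Statistical Analysis section and the analysis plan:

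1. Make at least one major complication within 12 months and at least one minor complication within 12 months the dependent variables of the predictor models, with any complication as a supporting model.
2. Prespecify the nine variables and fit them by penalised logistic regression (Firth or ridge, for example), in place of univariate screening and stepwise selection. Report bootstrap optimism-corrected discrimination and calibration.
3. Report each single complication as an incidence with an exact 95% CI. Model one only where its event count supports it, and label that model descriptive.

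Pooling alone does not guarantee enough events. The major-only model may stay below 10 per variable, which is why penalisation belongs in the fix.

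The cost is a change of wording and some analysis code, with no new data. The downside is that a composite mixes complications with different mechanisms. The table of single complications keeps those differences visible.
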